##### Propensity for β-adrenoreceptor blocking drug prescription

As participants prescribed β-adrenoreceptor blocking drugs are likely to have comorbidities, be older and have a high body mass index (BMI), a propensity score for β-adrenoreceptor blocking drug prescription will be calculated using a cumulative logit regression model and including demographic factors and relevant diagnoses at any time prior to β-adrenoreceptor blocking drug prescription (box 1).

Box 1List of potential variables to be included in the calculation of propensity score for β-adrenoreceptor prescriptionDemographic factors.Body mass index (WHO classification categories)*, smoking status* and deprivation score (general practice-level Index of Multiple Deprivation Score).Comorbidities.Hypertension, angina, myocardial infarction, congestive cardiac failure, atrial fibrillation, stroke, high cholesterol, chronic kidney disease, diabetes, anxiety, migraine, Charlson Comorbidity Index (excluding comorbidities in the propensity score) and duration in years of cardiovascular comorbidities prior to cohort entry.Drug prescriptions.Calcium channel blockers, ACE inhibitors, angiotensin II receptor antagonists, bendroflumethiazide, aldosterone antagonists, loop diuretics, alfa-adrenoreceptor blocking drugs, nitrates, nicorandil, aspirin, clopidogrel, statin, fibrate, vitamin K antagonists and non-steroidal anti-inflammatory drugs (in the progression cohort), and as a marker of severity of underlying disease at cohort entry the number of antihypertensive, antiarrhythmic or antianginal drugs prescribed in the 12-month period prior to cohort entry.*Categorised as missing if not available.

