##### Propensity for β-adrenoreceptor blocking drug prescription

This will be calculated as in cohort study 1. Additionally, propensity score will include hand osteoarthritis (interphalangeal or thumb base osteoarthritis—a marker of generalised osteoarthritis), neck pain or back pain, spinal degenerative diseases (indicating osteoarthritis in the spine—a marker of generalised osteoarthritis), arthroscopic knee or hip surgery, number of analgesic prescriptions between the first consultation for knee/hip osteoarthritis and β-adrenoreceptor blocking drug prescription, aspirin, statin and bisphosphonate, and glucosamine/chondroitin sulfate prescription in the 12-month period prior to cohort entry, as these may affect knee or hip osteoarthritis progression.^29–33^

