### Statistical analysis

Covariate balance between matched exposed and unexposed participants will be examined. Unbalanced covariates will be included in the model as separate covariates. Other covariates that do not influence exposure but influence outcomes or reflect health-seeking behaviour alone may be included in the model after evaluating their balance between exposed and unexposed groups. These are the following:

Number of GP consultations in the 12-month period preceding cohort entry.Number of hospital outpatient referrals in the 12-month period preceding cohort entry.Number of hospital admissions in the 12-month period preceding cohort entry.Total number of GP consultations for knee or hip injury prior to cohort entry.Non-osteoporotic fractures, defined as fractures in any bone except the femur, distal radius and vertebrae, after the age of 18 years but before the age of 50 years in women and 60 years in men. This is a surrogate for physically active occupation or lifestyle that may associate with incident osteoarthritis.

Participants will enter the cohort on the index date, and data will be censored at the earliest of an event, study end date (31 December 2017), date of death, transfer out of CPRD for all outcomes, and additionally date of the last prescription of β-adrenoreceptor blocking drugs, plus 4 weeks (usual duration of GP prescription in the UK) for incident osteoarthritis, incident knee or hip pain, or new analgesic prescription. Given the reported effects of propranolol on pain sensitivity in patients with fibromyalgia,^34^ we anticipate β-adrenoreceptor blocking drugs to have an analgesic effect in the short term, and outcome events >4 weeks after the date of the last β-adrenoreceptor blocking drug prescription will not be included in the analysis, except for total joint replacement which may be delayed due to a period of analgesia.

Time to event data in the exposed and unexposed groups will be compared using Kaplan-Meier survival curves. Schoenfeld residuals will be examined to see if survival curves meet the assumptions of the proportional hazard model. Cox proportional HRs and 95% CI will be calculated for each incident outcome using the first Read code for the event. Similarly, HRs will be calculated for new analgesic prescriptions, defined as prescription for NSAIDs, opioids, gabapentin and pregabalin, respectively, in those exposed to β-adrenoreceptor blocking drugs, with unexposed as the referent.

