The analysis will be stratified according to class of β-adrenoreceptor blocking drug used. A likelihood ratio test for interactions will be used to examine the hypothesis that the association between β-adrenoreceptor blocking medicines and incident osteoarthritis differs according to statin, aspirin or bisphosphonate prescription, as their use has been negatively associated with osteoarthritis.

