### Sample size

#### Incident knee osteoarthritis and hip osteoarthritis

The incidence of knee and hip osteoarthritis is 6.5 and 2.1 per 1000 person-years in primary care-based European populations >40 years in age.^1^ Previous research suggests that 6.14% of patients registered in the CPRD are on β-adrenoreceptor blocking drugs, with over two-thirds on treatment for >10 years.^38^ Thus, for a cohort with one exposed and four unexposed participants, the total sample size required to detect an HR of 0.70 for developing knee osteoarthritis and hip osteoarthritis is 88 273 (17 655 exposed) and 273 225 (54 645 exposed) participants, respectively, for a planned study with 80% power and 1% type I error.

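### Bisphosphonate prescription is a planned effect modifier for incident osteoarthritis but, unlike statin and aspirin, is missing from the Study 1 propensity list and covariates

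*Protocol article*

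**What the plan says.** Four places in the protocol article bear on this.

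- **Statistical analysis, interaction test.** A likelihood ratio test will examine whether the association of β-blockers with "incident osteoarthritis differs according to statin, aspirin or bisphosphonate prescription, as their use has been negatively associated with osteoarthritis". Incident osteoarthritis is the outcome of cohort study 1, and one reason is given for all three drugs.
- **Box 1, under the cohort study 1 propensity section.** The drug entries include "aspirin, clopidogrel, statin, fibrate, vitamin K antagonists and non-steroidal anti-inflammatory drugs (in the progression cohort"). Statin and aspirin are there; bisphosphonate is not. The title of the box presents its entries as candidates.
- **Cohort study 2, propensity section.** The score is extended by several items, among them "aspirin, statin and bisphosphonate, and glucosamine/chondroitin sulfate prescription in the 12-month period prior to cohort entry". The reason given is "as these may affect knee or hip osteoarthritis progression".
- **Statistical analysis, covariates.** Balance will be examined, and "Unbalanced covariates will be included in the model as separate covariates". A further list opens with "Other covariates that do not influence exposure but influence outcomes or reflect health-seeking behaviour alone may be included in the model". It has five items: GP consultations, outpatient referrals, hospital admissions, consultations for knee or hip injury, and non-osteoporotic fractures. Bisphosphonate is not one of them.

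**The concern.** The protocol treats three drugs alike when it explains why they might modify the β-blocker association with incident osteoarthritis, but not when it builds the Study 1 comparison. Statin and aspirin go into the Study 1 score. Bisphosphonate goes only into the score of the cohort in which incident osteoarthritis is not the outcome.

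A drug associated with the outcome confounds the main hazard ratio if its use also differs between exposed and unexposed participants after matching. The protocol supplies the first condition for bisphosphonate. For the second, Study 1 has no design step that would control a difference and no explicit commitment to look for one. Little else on the lists stands in for it: beyond matching on age and sex, no Study 1 variable names osteoporosis, and the one fracture covariate leaves out the femur, distal radius and vertebrae. At stake is a possible small bias in the main Study 1 hazard ratios, together with an avoidable mismatch between the variable lists and the interaction hypothesis.

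**Working it through.** **1. The lists side by side**

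| Drug | Interaction test, incident OA (Study 1) | Box 1 (Study 1 score) | Five further covariates | Added to Study 2 score |
|---|---|---|---|---|
| Statin | yes | yes | no | yes (restated) |
| Aspirin | yes | yes | no | yes (restated) |
| Bisphosphonate | yes | **no** | **no** | yes |

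The asymmetry is in the text and needs no assumption.

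**2. The plan's own figure**

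The Sample size section states that "the total sample size required to detect an HR of 0.70 for developing knee osteoarthritis and hip osteoarthritis is 88 273 (17 655 exposed"), with 80% power and 1% type I error. The inputs from that section are HR 0.70, one exposed to four unexposed (exposed fraction 0.2), and a knee osteoarthritis incidence of 6.5 per 1000 person-years. The Schoenfeld formula with a two-sided test gives

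events = (2.5758 + 0.8416)² / (0.2 × 0.8 × (ln 0.70)²) = 11.679 / 0.020355 ≈ 573.8, or 574 rounded up.

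Taking the incidence as the event probability over one person-year, 574 / 0.0065 = 88 308, which is within 0.1% of the stated 88 273. The figure reproduces. No covariate list enters the formula, so adding bisphosphonate leaves the stated sample size as it is. The calculation serves here only to fix the target HR of 0.70 as the yardstick.

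**3. How much could the omission matter?**

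The protocol gives neither the frequency of bisphosphonate use nor its hazard ratio for osteoarthritis, so the inputs below are assumptions. Let h be the bisphosphonate hazard ratio, p1 the proportion of users among the exposed, and p0 the proportion among the unexposed. For a rare outcome, with use unrelated to the other covariates, the β-blocker hazard ratio is multiplied by about

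B = (1 + p1(h − 1)) / (1 + p0(h − 1)).

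| p0 | p1 | h = 0.5 | h = 0.7 | h = 0.8 |
|---|---|---|---|---|
| 2% | 1% | 1.005 | 1.003 | 1.002 |
| 2% | 3% | 0.995 | 0.997 | 0.998 |
| 5% | 3% | 1.010 | 1.006 | 1.004 |
| 5% | 8% | 0.985 | 0.991 | 0.994 |
| 10% | 5% | 1.026 | 1.016 | 1.010 |
| 10% | 15% | 0.974 | 0.985 | 0.990 |

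The two extremes, worked out:

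- (1 − 0.05 × 0.5) / (1 − 0.10 × 0.5) = 0.975 / 0.950 = 1.026
- (1 − 0.15 × 0.5) / (1 − 0.10 × 0.5) = 0.925 / 0.950 = 0.974

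Applied to the target, 0.70 × 0.974 = 0.68 and 0.70 × 1.026 = 0.72. If use is the same in both groups, B = 1 and there is no bias.

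**4. The interaction test**

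A standard likelihood ratio test for interaction compares models that both contain the main effect of the modifier. That analysis would therefore adjust for bisphosphonate. The gap concerns mainly the main Study 1 hazard ratios, where no such term is planned.

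**The case against.** The strongest reply is that nothing shows an actual imbalance. Controls are matched on age band, sex, practice, registration year and propensity score, and leaving a variable out of a score does not make it unbalanced. Box 1 is presented as a list of candidates, and the rule on unbalanced covariates is not restricted to it. The Study 2 additions are justified by progression, so the two lists need not be identical. The numerical effect is slight on any plausible input.

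Much of this stands, and it rules out four stronger readings that a reader might infer.

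- **That the Study 1 groups are left unbalanced on bisphosphonate.** This would need use to differ by β-blocker status after matching, and the protocol says nothing on that.
- **That an imbalance would go unseen.** The balance check is worded generally. Bisphosphonate is not named for it, but neither is it excluded.
- **That the interaction test is invalid, or that most matched sets would lack a control on bisphosphonate.** Estimating effect modification does not require the modifier to be balanced between groups. How many sets lack a user reflects how rare the drug is; it would look much the same with equal use in both groups or with the drug added to the score. The protocol also does not say that the Cox model is stratified by matched set.
- **That the protocol calls bisphosphonate protective.** It reports a negative association, which is weaker.

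The reply does not remove the inconsistency. A list of candidates allows its entries to be dropped; it does not bring in a drug that is not on it. The progression rationale explains why bisphosphonate is in Study 2, not why it is absent from Study 1, where the protocol gives a separate reason tied to incident osteoarthritis. Nor is this detail left to a fuller document: the article prints explicit variable lists, and they do not match its own interaction plan.

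**Conclusion.** The point holds in a limited form. The protocol regards bisphosphonate prescription as related to incident osteoarthritis on the same ground as statin and aspirin, yet places only those two in the Study 1 propensity list and leaves bisphosphonate out of the further covariates as well. Its balance in Study 1 is neither secured by design nor explicitly promised a check. Whether an imbalance exists cannot be told from the document.

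If there is one, the main hazard ratio would be shifted by a factor of roughly 0.97 to 1.03. This rests on assumed use of 2% to 10% in the unexposed and 1% to 15% in the exposed, paired as in the table, and on an assumed bisphosphonate hazard ratio of 0.5 to 0.8. That is small against a target of 0.70. The point is a minor improvement to the plan and does not threaten its conclusions.

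**What to change.** Add bisphosphonate prescription in the 12 months before the index date, the window named for Study 2, to the Study 1 propensity score and to the Study 1 balance table. If it remains unbalanced after matching, enter it in the Cox model under the existing rule. For the three interaction tests, define statin, aspirin and bisphosphonate use at baseline, before the index date, and keep the main effect of each drug in the model. If bisphosphonate was left out of Study 1 on purpose, give the reason.

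The cost is one variable from prescription data that Study 2 already requires. The stated sample size does not change, and there is no meaningful drawback.

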##### Exclusion criteria

Exclusion criteria will be consultation for any of the following prior to the index date:

Osteoarthritis at any joint.Knee, hip, neck or back pain.Conditions causing joint damage or chronic pain: autoimmune inflammatory rheumatic diseases, such as rheumatoid arthritis, psoriatic arthritis, ankylosing spondylitis, lupus, polymyalgia rheumatica, gout, radiculopathy, neuropathy and fibromyalgia.Contraindications to prescription of β-adrenoreceptor blocking medicines: chronic obstructive pulmonary disease, asthma, peripheral vascular disease, heart block, aortic stenosis and hypertrophic obstructive cardiomyopathy.Two consecutive prescriptions for any opioid, any NSAID, gabapentin, pregabalin, duloxetine or amitriptyline prior to the index date.<1 year up-to-standard registration prior to index date to reduce the risk of prevalent cases (eg, with osteoarthritis) being classified as incident cases.^28^

The cohort entry date will be the index date. The unexposed participants will be allocated the index date of their matched exposed participant.

The cohort exit date will be the earliest of the date of the last prescription of β-adrenoreceptor blocking drug prescription, plus 4 weeks or a matched pseudo-exit date for the matched controls, date of the first outcome, date of death, transfer-out date, date of the last data collection or study end date (31 December 2017).

#### Cohort study 2

Cohort study 2 will be on β-adrenoreceptor blocking drug prescription and total joint replacement and analgesic use. The exposure will be as in cohort study 1.

The outcome will be total knee replacement (primary), total hip replacement and analgesic prescription: (1) NSAIDs, (2) opioids, (3) gabapentin or pregabalin, and (4) amitriptyline.

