**Methods and analysis:**

This is a cohort study using data from the Clinical Practice Research Datalink. Two separate analyses will be performed. Study 1 will be on the association between β-blocker prescription and incident knee/hip osteoarthritis. Inclusion criteria will be age ≥40 years. Exposed participants will be those with ≥2 continuous β-blocker prescriptions, and the index date will be the date of the first prescription of β-blocker. Unexposed participants will include up to four controls matched for age, sex, general practice surgery and propensity score for β-blocker prescription. Exclusion criteria will include contraindications to β-blockers, consultations for osteoarthritis or potent analgesic prescription before the index date. Outcomes will be knee osteoarthritis (primary outcome), hip osteoarthritis, knee pain and hip pain. Study 2 will be on the association between β-blocker prescription and total joint replacement and analgesic prescription in people with osteoarthritis. Inclusion criteria will be age ≥40 years, knee or hip osteoarthritis, and index date will be as in study 1. Unexposed participants will be as in study 1, additionally matched for consultation for knee or hip osteoarthritis prior to the index date. Exclusion criteria will include contraindications to β-blockers and osteoarthritis in other joints prior to the index date. Outcomes will be total knee replacement (primary outcome), total hip replacement and new analgesic prescription.

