### Study population

All CPRD registered participants contributing acceptable quality data in up-to-standard general practices (GP) between 1 January 1990 and 31 December 2017 are included. Two separate cohort studies will be performed.

#### Cohort study 1

Cohort study 1 will be on β-adrenoreceptor blocking drug prescription and incident osteoarthritis. Exposure will be ≥2 continuous prescriptions for β-adrenoreceptor blocking drugs, and will be further categorised according to duration of treatment (≤6 months, 7–12 months, 12–24 months and >24 months). The outcomes will be knee osteoarthritis (primary), hip osteoarthritis, knee pain and hip pain.

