###### Unexposed

Age (5-year age band based on year of birth), sex, GP surgery, year first registered in CPRD (±1 year) and propensity score for β-adrenoreceptor blocking drug prescription matched to the exposed participants.

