##### Exclusion criteria

Exclusion criteria will be previous consultation for any of the following prior to the first prescription of β-adrenoreceptor blocking drug:

Osteoarthritis at any other joint.Neck or back pain.Conditions associated with joint damage or chronic pain (as above).Conditions contraindicating prescription of β-adrenoreceptor blocking medicines (as above).Previous knee or hip replacement.Knee or hip joint replacement within 3 months of the date of the first β-adrenoreceptor blocking drug prescription or matched index date in the unexposed participants. These will be excluded because we do not expect β-adrenoreceptor blocking drug prescription to reduce total joint replacement rates immediately and may be commenced during preanaesthetic check-up.<1 year up-to-standard registration prior to the first qualifying prescription of β-adrenoreceptor blocking drug.^28^
Additionally, participants who receive two consecutive prescriptions for opioids, NSAIDs, gabapentin, pregabalin, duloxetine or amitriptyline prior to the index date will be excluded from the cohort when examining the association between β-adrenoreceptor blocking drug prescription and new analgesic prescription.

The cohort entry and exit dates will be as in cohort study 1. Nearest neighbour matching (±0.2 SD) will be used to match exposed to unexposed participants.

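### Outcome records made on the index day pass the exclusions yet fall inside follow-up, mainly in the exposed; this biases the HR upwards for OA, pain and new analgesics, but not for joint replacement

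*Protocol article*

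**What the plan says.** In the abstract (Methods and analysis), "the index date will be the date of the first prescription of β-blocker". Under Cohort study 1, Exclusion criteria: "Exclusion criteria will be consultation for any of the following prior to the index date". The list that follows includes OA at any joint and knee or hip pain. The same section adds "The cohort entry date will be the index date", and for controls "The unexposed participants will be allocated the index date of their matched exposed participant".

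Controls are matched on "Age (5-year age band based on year of birth), sex, GP surgery, year first registered in CPRD (±1 year) and propensity score"; a consultation on or near the assigned date is neither a matching factor nor an eligibility condition.

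For study 1, "The outcomes will be knee osteoarthritis (primary), hip osteoarthritis, knee pain and hip pain". The Statistical analysis section says "Participants will enter the cohort on the index date, and data will be censored at the earliest of an event" and dates each incident outcome by its first Read code, with no minimum time after entry.

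For the new-analgesic outcome in study 2, people with two consecutive analgesic prescriptions "prior to the index date will be excluded from the cohort when examining the association". The only lag in the article is in the study 2 exclusions: joint replacement within 3 months of the index date, in either group.

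**The concern.** Eligibility looks back to the day before the index date, and time at risk starts on the index date, so that day belongs wholly to follow-up. It is not an ordinary day for the exposed, because a prescription was issued. For controls it is a copied calendar date.

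A patient who mentions knee pain when the β-blocker is started, or who receives a first NSAID or opioid that day, passes the exclusions and has an event at time zero. The symptom came before any dose. A control can have such an event only if they happened to attend on that date. Existing symptoms would be counted as incident outcomes, almost entirely in the exposed, and the HR would be pushed up.

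The article's own aims point the same way. It requires a year of registration so that prevalent cases are not mistaken for incident ones. It also excludes early joint replacements, partly because the drug may be started at a pre-operative check. OA, pain and analgesic outcomes get no such protection. Adjusting for the previous year's GP consultations is optional and concerns contact before entry, so it does not correct an excess on the entry day.

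**Working it through.** **The plan's own figure.** Inputs from the Sample size section: HR 0.70, one exposed to four unexposed, 80% power, 1% type I error (two-sided is the version that reproduces), knee OA incidence 6.5 per 1000 person-years.

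- Events = (2.576 + 0.842)² / (0.2 × 0.8 × (ln 0.70)²) = 573.8.
- N = 573.8 / 0.0065 = 88 273, of whom 17 655 are exposed. This matches the article.
- Dividing by an annual rate implies one year of follow-up per person.

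The sample size is not in dispute; it gives a base for sizing the bias.

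**Size of the index-day excess.** Let r be the outcome rate, v the visits per year and F the mean follow-up in years. Assume that codes arise only at visits, that all visits are equally likely to produce one, and that each exposed person has one visit on the index day. The article gives none of these.

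- Probability of a code at one visit = r/v.
- Expected exposed events over follow-up with no drug effect = rF.
- Proportional excess = (r/v)/(rF) = 1/(vF), so the apparent HR is about 1 + 1/(vF) under no effect.
- The index-day term does not depend on the drug, so a true HR of 0.70 appears as about 0.70 + 1/(vF).

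With v = 6:

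| Mean follow-up F (years) | Excess in exposed events | Apparent HR if true HR is 1 | Apparent HR if true HR is 0.70 |
|---|---|---|---|
| 1 | 1/6 = 17% | 1.17 | 0.87 |
| 2 | 1/12 = 8% | 1.08 | 0.78 |
| 5 | 1/30 = 3% | 1.03 | 0.73 |
| 10 | 1/60 = 2% | 1.02 | 0.72 |

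At F = 0.5, the upper edge of the shortest treatment-duration category, the excess is 1/3 = 33%.

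If only a share p of first prescriptions come with a consultation, each excess is multiplied by p. For example, p = 0.5 halves every figure in the second column.

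**Counts for knee OA at the planned size.**

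- Controls: 88 273 − 17 655 = 70 618. Expected index-day events = 70 618 × 0.0065 / 365.25 = 1.3.
- Exposed: 17 655 × 0.0065 / v = 38, 19 and 12 for v = 3, 6 and 10.
- For scale, one year gives 17 655 × 0.0065 = 115 exposed events at HR 1, and 0.70 × 115 = 80 at HR 0.70.

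**The case against.** **Time-zero events may be dropped.** The article has no rule for zero-length follow-up, and some survival software discards such records. A condensed article can leave this to a fuller document. So a reader may not infer that the plan expressly counts these events; that is only the literal reading. But the stated rule admits the records, and the result should not depend on a software default.

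**Follow-up may be long.** The Sample size section cites over two-thirds of users treated for more than 10 years, which implies a mean of at least 2/3 × 10 = 6.7 years and an excess of 1/(6 × 6.7) = 2.5%. That figure describes existing users, and follow-up in new starters that ends at the first event or censoring date may be shorter, so the whole range must be shown. The reduction with long follow-up stands.

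**Larger figures are tempting.** Three initiation visits at F = 2 would give 3/12 = 25%, an HR of 1.25. Two of those visits fall after the index day; they are extra surveillance after initiation, a different mechanism that a change to the index-day rule does not remove. Likewise, the 115 − 80 = 35 events that would erase an HR of 0.70 for knee OA presuppose one year of follow-up and a visit rate near the low end of the range. The article does not support either figure as the expected bias.

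**Knee OA is less vulnerable.** People with any earlier knee, hip, neck or back pain consultation are excluded, and the Sensitivity analyses section says OA codes may come only after several pain consultations. A first knee OA code on the index day should then be uncommon, and the equal-visits assumption probably overstates it. This stands.

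**A prescription is not always a consultation.** This stands too; it reduces the size but does not change the direction.

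**Conclusion.** The point holds for incident OA, knee and hip pain, and new analgesic prescription. Read literally, the rules place index-day records inside follow-up, where they accrue mainly to the exposed, and the bias is towards a higher HR.

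The excess is about 17%, 8%, 3% and 2% at mean follow-up of 1, 2, 5 and 10 years, given 6 visits a year, one index-day visit per exposed person and equal coding probability at every visit. It is likely to matter most for pain and analgesics and for the category of 6 months or less. There, a concentration of early events could also look like a benefit that grows with duration. It is probably smaller for knee OA.

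A reader might extend the point to every outcome. The documents do not support that: total knee replacement, the primary outcome of study 2, and hip replacement have the 3-month exclusion in both groups.

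**What to change.** In both groups, exclude anyone with an outcome code or outcome drug recorded on or before the index date for the outcome being analysed, and start time at risk the following day. For analgesics the wording needs care. The present rule requires two consecutive prescriptions, so moving its window by a day would still admit a single first prescription issued on the index date; the rule should name any outcome drug on that date.

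Optionally, add a sensitivity analysis that drops events in a short, prespecified early window in both groups. It would address extra visits after initiation, which the index-day change leaves in place. The window length is for the investigators to justify; the article gives no lag for these outcomes.

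The cost is a change of wording, possibly one extra run, and the loss of a small number of early events. No new data are needed, and the planned 574 events and 88 273 participants are unchanged.

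### Study 1 does not list previous knee or hip replacement as an exclusion, so a person with a recorded replacement but no earlier osteoarthritis or joint-pain consultation can enter as disease-free

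*Protocol article*

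**What the plan says.** The exclusions for Cohort study 1 are introduced with "Exclusion criteria will be consultation for any of the following prior to the index date". The list starts with "Osteoarthritis at any joint.Knee, hip, neck or back pain.Conditions causing joint damage or chronic pain" and goes on to named inflammatory and pain conditions and contraindications to β-blockers. It also contains "Two consecutive prescriptions for any opioid, any NSAID, gabapentin, pregabalin, duloxetine or amitriptyline prior to the index date". The last item requires at least one year of up-to-standard registration, with the stated purpose "to reduce the risk of prevalent cases (eg, with osteoarthritis) being classified as incident cases". Joint replacement appears nowhere in this list, nor in the abstract's summary of the Study 1 exclusions.

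The exclusions for Cohort study 2 refer back to Study 1 for the shared pain conditions and contraindications, and then add a separate item, "Previous knee or hip replacement". In that study, "The outcome will be total knee replacement (primary), total hip replacement and analgesic prescription".

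The primary outcome of Study 1 is knee osteoarthritis. Hip osteoarthritis, knee pain and hip pain are the other outcomes. Under Statistical analysis, each incident outcome is dated by its first Read code.

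**The concern.** Study 1 estimates a hazard ratio for new osteoarthritis, so everyone should be free of the disease at entry. A knee or hip replacement is strong evidence that the disease was already there. The protocol excludes osteoarthritis at any joint, so a replaced hip matters for the knee outcome too.

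The existing criteria look for consultations and prescriptions, not procedures. Osteoarthritis that was managed years ago, or at another practice, may survive in the record only as a procedure or history code. One year of registration does not guarantee that the earlier consultations are visible. Such a person meets every listed criterion.

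Two errors follow. A later code for osteoarthritis or pain, in the replaced or the opposite joint, is counted as a first event although the disease is old. And a person with both knees replaced contributes knee-osteoarthritis person-time without being at risk. The first error can move the hazard ratio; the second costs a little power.

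**Working it through.** **Comparison of the two lists.**

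| Item before index | Study 1 | Study 2 |
|---|---|---|
| Osteoarthritis | excluded at any joint | knee or hip required; other joints excluded |
| Knee or hip pain | excluded | not excluded |
| Two consecutive analgesic prescriptions | excluded | excluded only for the analgesic outcome |
| Under one year of registration | excluded | excluded |
| Previous knee or hip replacement | **not listed** | excluded |

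The gap in Study 1 is therefore limited to people who have a replacement on record and none of the other items.

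**The plan's own figure.** The Sample size section uses HR 0.70, 1% type I error, 80% power, one exposed to four unexposed, and a knee incidence of 6.5 per 1000 person-years. Schoenfeld's formula, two-sided, gives events = (2.576 + 0.842)² / (0.2 × 0.8 × (ln 0.70)²) = 574. Then 574 / 0.0065 = 88,308, against the stated 88 273. The figure reproduces, if the yearly incidence is taken as the event probability, and this point does not show it to be wrong.

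**Effect on the hazard ratio.** The protocol does not say how many such people there are or how often they are coded later. Both inputs are assumptions:
- p, their share of each group, the same in exposed and unexposed: 0.2% to 1%
- r, their rate of a first knee code relative to everyone else unexposed: 5 to 10
- no drug effect on the coding of disease that already exists

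Observed HR = (0.70(1 − p) + pr) / ((1 − p) + pr).

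| p | r | Calculation | Observed HR |
|---|---|---|---|
| 0.2% | 5 | (0.6986 + 0.010) / (0.998 + 0.010) | 0.703 |
| 0.2% | 10 | (0.6986 + 0.020) / (0.998 + 0.020) | 0.706 |
| 1% | 5 | (0.693 + 0.050) / (0.990 + 0.050) | 0.714 |
| 1% | 10 | (0.693 + 0.100) / (0.990 + 0.100) | 0.728 |

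Their share of unexposed events is pr / (1 − p + pr). This runs from 0.010 / 1.008 = 1.0% to 0.100 / 1.090 = 9.2%.

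**Other assumptions about the same people.**
- If the drug effect applies to them as well, an equal share in both groups leaves the HR at 0.70.
- If they can never have the event, an equal share again leaves the HR at 0.70, and only information is lost. At a 0.5% share power falls from 80% to 79.8%, and at 1% to 79.5%. Restoring it at 1% needs 88,273 / 0.99 = 89,165 participants.

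**The case against.** The strongest reply is that the gap is nearly closed already. Study 1 removes anyone with a consultation for osteoarthritis at any joint, or for knee, hip, neck or back pain, at any time before index, as well as people with repeated analgesic prescriptions. Few people reach a joint replacement without leaving one of these traces, and some replacements follow a fracture rather than osteoarthritis. This stands. It limits the size of the problem, and the protocol does not show that such people are in fact present; it shows only that the criteria would admit them.

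It can also be said that this is a condensed article whose code lists might group replacement with osteoarthritis. That is possible. But the list is itemised in detail, and Study 2 states replacement as an item of its own, which points the other way.

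Two stronger readings are tempting, and the protocol does not support them:
- **That the two studies contradict each other.** In Study 2 replacement is the outcome and osteoarthritis is an entry condition, so the exclusion there mainly keeps people at risk of a first replacement. The lists need not match. The contrast shows only that the item can be defined in these data.
- **That the bias differs between groups**, because Study 2 remarks that β-blockers "may be commenced during preanaesthetic check-up". That remark explains a different Study 2 rule, on replacement within three months of the first prescription. A drug started at such a check-up comes before the operation, so it concerns surgery after index. The people at issue here had surgery before index, often long before. Matching on practice and year of registration should also give both groups a similar look-back. There is no basis for assuming that these people are commoner among the exposed, or for carrying the three-month rule into Study 1.

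**Conclusion.** The point holds as a minor one. The Study 1 criteria, as written, admit people with a recorded knee or hip replacement and no earlier osteoarthritis or joint-pain consultation, which works against the section's own purpose.

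The effect does not need any imbalance between the groups. If existing disease is coded regardless of β-blocker use, an equal share in both groups pulls the HR towards 1: a true 0.70 reads about 0.70-0.73 at a 0.2-1% share and 5-10 times the background rate. If the drug effect applies to these people too, or they cannot have the event, the HR does not move and at most about half a percentage point of power is lost at a 1% share. All these shares and rates are assumptions; the true size cannot be derived from the protocol. No stated figure is wrong, and the study's conclusions are unlikely to turn on this.

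**What to change.** Add previous knee or hip replacement before the index date to the Study 1 exclusion list. Apply it to exposed and unexposed participants, using the matched index date for the unexposed and the same definition as in Study 2. If the full protocol's code list already counts replacement as osteoarthritis, it is enough to say so in the criteria.

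The cost is one line of text and the loss of a small number of participants. The number can be counted when the cohort is built and reported with the other exclusions.
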